### Sample Size

The primary outcome is the percentage share of the monthly household food expenditure from supermarkets. With reference to a previous study on supermarkets and food purchasing in Kenya [18], a baseline sample of 250 households—125 intervention and 125 comparison households—was estimated to allow the detection, with 95% confidence and 80% power, of a difference between intervention and comparison groups of 5% in expenditure share, while allowing for a 50% attrition rate between baseline and follow-up. Therefore, we aimed to recruit 300 households at baseline in 2019 to ensure adequate statistical power. While we did not anticipate 50% attrition, we used this as an upper limit to ensure we recruited an adequate number of households at baseline.

### Sampling and Recruitment

#### Household Survey

In each of the study areas, we consulted with local community health volunteers. In the Kenyan health system, community health volunteers represent the first basic level of care. The majority of these volunteers have completed 8 years of primary education and are elected or nominated by their communities to serve them in a voluntary capacity on health-related matters under the community health strategy [21]. A community health volunteer typically works in a village with about 100 households and is supervised by community health extension workers, who are government employees [22]. Community health volunteers visit households monthly to collect general health indicators and often work with partners in their respective areas. They are assumed to know the households well in terms of living standards.

We engaged with 20 community health volunteers from the intervention area and 20 from the comparison area. Each community health volunteer provided a household list from their area, for a total of about 2000 households per study area. In addition, community health volunteers classified each household as low, medium, or high SES. These classifications were broadly based on asset-based measures used in previous household surveys conducted in LMICs [23], in particular, focusing on housing characteristics (eg, material of dwelling floor and roof and main cooking fuel) and access to basic services (eg, electricity supply, source of drinking water, and sanitation facilities), modified for the local context.

Using a geographic information system (GIS), we plotted a quadrant from the center of each study area to demarcate the area into four subareas—northeast, northwest, southeast, and southwest— and plotted three radii of 500 m, 1 km, and 2 km from the center. Each household in the sampling frame was classified by quadrant, distance from the center, and SES. A stratified random sample of households was drawn from these three strata—400 in total (200 in the intervention area and 200 in the comparison area)—to account for refusal to participate.

Study teams consisting of two field workers, guided by a local community health volunteer, will knock at the doors of eligible households to make an initial approach and recruit households to participate in the household survey.

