**Figure 1 figure1:**
[figure not shown]
Images showing (a and b) the Lake Basin Mall site, (c) a scene from within the mall, and (d) the hypermarket site.

The opening of the hypermarket provides an opportunity to examine potential impacts on dietary behaviors among residents of Kisumu living nearby and on the local foodscape, using a natural experimental design [19], as well as the opportunity to explore whether impacts are distributed unequally or inequitably. Impacts will be examined relative to the town of Homabay in Homabay County, a neighboring comparison area where no hypermarket is planned. As such, the overall purpose of this study is to address the following research questions:

What are the individual, household, and population impacts of the new hypermarket at Lake Basin Mall on food shopping practices, dietary behaviors, physical activity patterns, and body composition among local residents across different SES groups?How has the local foodscape changed, do these changes relate to the new hypermarket at Lake Basin Mall, and how are they experienced by local residents?

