### Analysis Methods

#### Household Survey

For all quantitative analyses, the level of statistical significance will be set as α<.05. All participants who provide data will be included in analyses, and we will not impute missing data. Net changes between baseline and follow-up will be computed, and significance tests will be conducted using a method appropriate to the distribution of the data. Differences in means will be compared using *t* tests or analyses of variance for normally distributed variables, while medians will be compared using the Wilcoxon rank-sum test or the Kruskal-Wallis test for skewed data. We will further undertake multivariable regression analyses adjusted for important covariates, using models appropriate to the distribution of the data and accounting for clustering by household. For binary outcomes, we will explore the use of logistic regression models, and for continuous outcomes we will consider linear regression models and negative binomial or zero-inflated generalized linear models. Regression estimates and 95% confidence intervals will be reported.

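### The unadjusted tests of individual-level outcomes ignore household clustering, so their p values are modestly too small; the household outcomes and the reported regression intervals are not affected

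*Protocol article*

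**What the plan says.** Under Sampling and Recruitment (Household Survey), community health volunteers listed about 2,000 households per area. "Each household in the sampling frame was classified by quadrant, distance from the center, and SES". The article continues: "A stratified random sample of households was drawn from these three strata", giving "400 in total (200 in the intervention area and 200 in the comparison area"). How the 200 per area were allocated across strata is not stated.

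Under Eligibility, as many as 5 adults in a household may complete the questionnaires and measurements. Table 1 reports 376 households (180 and 196) and 516 individuals (260 and 256).

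Under Analysis Methods (Household Survey), for all quantitative analyses "the level of statistical significance will be set as α<.05". Changes are then tested with t tests or ANOVA if normally distributed, and with rank-sum or Kruskal-Wallis tests if skewed. As a further step, covariate-adjusted regressions are fitted "using models appropriate to the distribution of the data and accounting for clustering by household". The 95% confidence intervals promised are those of the regressions.

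Under Outcomes, expenditure share, total food expenditure and food security are household measures. Dietary diversity, BMI and well-being are individual measures and are secondary.

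**The concern.** The four named tests, in their usual form, assume independent observations. Adults who share meals and money, which is how the article defines household members, are likely to resemble each other in diet, weight and well-being. Because whole households belong to one area or the other, positive correlation within households makes the true variance of an area difference larger than these tests assume.

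This is more than a missing detail. The article recognises the dependence and provides for it in the regressions, but it selects the unadjusted tests by distribution alone and does not call them descriptive. The same individual outcome can therefore be tested twice at the .05 level, with only one of the tests valid for clustered data. At stake is a somewhat raised false-positive rate for three secondary outcomes, and possible disagreement between the two tests for a reason that has nothing to do with confounding.

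**Working it through.** **Where clustering does not enter.** The plan's own figure is 250 households, to detect "with 95% confidence and 80% power, of a difference between intervention and comparison groups of 5% in expenditure share", with 50% attrition. The SD is not given. With n per group = 2(1.96 + 0.842)² SD²/5²:

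- An assumed SD of 9.9 gives 62 completers, 62/0.5 = 124 at baseline and 248 in total.
- An assumed SD of 10 gives 63, 126 and 252.

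So 250 is consistent with an SD of about 10. The outcome has one value per household, so the household design effect is 1 and the figure does not change.

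**Where it does enter.** Inputs from Table 1: 516 people in 376 households. Assumptions: an intra-household correlation (ICC) of 0.05 to 0.5, two-sided 5% tests, at least one respondent per household, and an exposure shared by the whole household (area).

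Formulas:
- Design effect: DEFF = 1 + (m − 1) × ICC
- True type I error: 2 × [1 − Φ(1.96/√DEFF)]

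Three values of m, because the article gives no distribution of respondents per household:
- Mean size: 516/376 = 1.37.
- Size-weighted (Σm²/Σm), most even split: 236 households with one person and 140 with two (236 + 280 = 516), so (236 + 140 × 4)/516 = 1.54.
- Size-weighted, most uneven split: 341 households with one person and 35 with five (341 + 175 = 516), so (341 + 35 × 25)/516 = 2.36.

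| ICC | m = 1.37: DEFF, true alpha | m = 1.54: DEFF, true alpha | m = 2.36: DEFF, true alpha |
|---|---|---|---|
| 0.05 | 1.02, 5.2% | 1.03, 5.3% | 1.07, 5.8% |
| 0.3 | 1.11, 6.3% | 1.16, 6.9% | 1.41, 9.9% |
| 0.5 | 1.19, 7.2% | 1.27, 8.2% | 1.68, 13.0% |

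The column for the mean size is slightly optimistic. With whole-number household sizes, the size-weighted value cannot fall below 1.54.

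**Stratification.** The three stratifiers give up to 4 × 3 × 3 = 36 cells per area, or 200/36 = 5.6 sampled households per cell. After recruitment this is 376/72 = 5.2, and at the 50% attrition that the article takes as its upper limit it is 2.6. A model with all cells crossed is therefore not practical.

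**The case against.** The strongest reply is that inference will rest on the regressions. They account for household clustering, they come after the simple tests, and theirs are the intervals to be reported. This is largely right, and it disposes of one tempting reading: that the reported individual-level intervals are too narrow. They are not. What remains is that the simple tests are planned as significance tests and nothing in the article demotes them.

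A second reply is that the size rests on assumed correlations. This also stands. The outcomes are changes, and the article gives no within-household correlation of changes. At the low end the excess is negligible.

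A reader might also infer that the sample is unrepresentative and must be weighted, because the first research question asks "What are the individual, household, and population impacts of the new hypermarket at Lake Basin Mall" and the analysis section mentions neither strata nor weights. The article does not support this:

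- It does not rule weights out, and its covariates are unnamed. A condensed article commonly leaves such detail to the full protocol or analysis plan.
- If allocation was proportional, the sample as drawn is self-weighting. Over-representation of any band or SES group is not shown, and a numerical bias could be produced only by inventing the allocation and the effects by stratum.
- Response was 180/200 = 90% in Kisumu and 196/200 = 98% in Homabay. These are rates by area and say nothing about non-response within strata.
- Ignoring strata under proportional allocation tends to make standard errors too large, the opposite direction from the clustering problem.

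**Conclusion.** The point holds in a limited form. As written, the unadjusted tests of dietary diversity, BMI and well-being do not allow for household clustering, and their p values are too small when the exposure is shared within the household. For an ICC of 0.05 to 0.5, true type I error is about 5.2% to 7.2% at the mean household size, and up to about 13% in the extreme case of ICC 0.5 with the most uneven sizes. The ICC and the spread of household sizes are assumptions. Comparisons on the individual-level dose (whether a person shops at the hypermarket) can vary within a household, so these figures do not carry over to them directly.

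The expenditure-share primary outcome, the other household outcomes, the sample size and the regression intervals are not affected. No bias in population estimates is established. The unstated allocation is a matter for clarification.

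**What to change.** In Analysis Methods (Household Survey), add wording to this effect:

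> Every comparison of an individual-level outcome, including unadjusted ones, will allow for clustering by household (an unadjusted regression with household-clustered robust errors or, for skewed outcomes, a clustered rank test).

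The alternative is to label the unadjusted tests descriptive and state that inference is taken from the clustered regressions.

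Secondary changes:
- State how the 200 households per area were allocated across quadrant, distance band and SES.
- Include the SES stratum as a covariate, with distance band and quadrant nested within area, where cell sizes allow. Nesting is needed because the comparison area is centred on a different landmark, so a band or quadrant does not mean the same thing in both towns.
- Use design weights for area-level population estimates only if allocation was disproportionate.

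The cost is slightly larger p values for three secondary outcomes and a little more analysis work. No new data are needed, since household membership and the strata are already recorded, and the follow-up analysis was still to come when the article was written.

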#### Focus Groups

Following completion of the household survey, a purposive sample of participants will be drawn for the resident focus groups. We will aim for a diverse sample that mirrors the basic demographic characteristics of the survey sample and includes a mixture of lower- and higher-SES participants, those living in formal and informal settlements, both males and females, and a range of ages. Householders will be approached and recruited by the same field worker teams using contact details provided during the household survey. We aim to conduct four focus groups in each study area, split by gender and SES.

#### Stakeholder Interviews

We will use existing relationships combined with snowball sampling to identify and recruit a range of stakeholders to participate in semistructured interviews, including mall developers and managers as well as members of the county government, including the trade executive, the health executive, the planning executive, and the local ward representative. We will give preference to those directly involved in the decision making and development of the mall and aim to interview at least 6 stakeholders per study area.

#### Shopper Intercept Survey

Once the hypermarket is open, a minimum of 20 shoppers will be recruited while they shop to answer a short survey.

### Assessment

#### Household Survey

At baseline and follow-up, participants will complete a household and an individual questionnaire. The household questionnaire will be completed by the head of household and by the person who is usually responsible for food purchasing and will assess the following variables:

Demographic variables for each individual in the household (ie, age, sex, relationship to head of household [eg, wife or child], ethnicity, education, and occupation).Characteristics of the household (ie, housing tenure and quality, access to electricity and water, appliance used for cooking, refrigerator ownership, car ownership, and duration of residence in the area).Household food purchasing in the previous month, including sources of food, types of food retail accessed, and amount of money spent at different types of food retailers and overall.Number of trips made to purchase food and modes of transport used in the previous month.Household food security, based on the Food and Agriculture Organization’s Food Insecurity Experience Scale [24].

The individual questionnaire will be completed by each eligible adult, aged 18 years or over, and will assess the following variables:

Dietary diversity using an unquantified 24-hour dietary recall and following the approach described by the Food and Agriculture Organization and the United States Agency for International Development’s Food and Nutrition Technical Assistance III Project [25]. In order to calculate a dietary diversity score, the range of foods and drinks consumed will be classified into 10 core food groups: grains, white roots, tubers, and plantains; pulses; nuts and seeds; dairy; meat, poultry, and fish; eggs; dark green leafy vegetables; other vitamin A–rich fruit and vegetables; other vegetables; and other fruit.Physical activity, using the World Health Organization Global Physical Activity Questionnaire [26].Well-being, using two items from the abbreviated version of the World Health Organization Quality of Life instrument [27].Social connectedness, using 3 items from the Social Provisions Scale [28].

Following this, all eligible participants in the household, both adults and children, will complete anthropometric measurements (ie, height, weight, and waist circumference) using standard procedures. A tape measure, stadiometer, and calibrated scales will be used. Each measurement will be taken in duplicate.

Assessments will last approximately two hours and will be conducted on different days of the week in order to capture both weekdays and weekends on the dietary recall. Although, ideally, multiple dietary recalls would be used, in order to minimize participant burden we will undertake a single dietary recall to describe the range of food groups consumed on the recall day. A field worker will administer questionnaires by interview with the aid of an electronic tablet, preprogrammed with prompts and validation rules to help limit missing data and ensure data quality. All field workers will be educated at the degree level in a related field (eg, health sciences) and will attend a minimum of five days of training covering all elements of the primary data collection, including a dedicated session on administering dietary recalls facilitated by a nutrition researcher. Following the training, field workers will have access to bespoke training resources.

#### Focus Groups

At baseline and follow-up, focus groups will be oriented around understanding what influences people’s food practices and exploring the role of the hypermarket within the local foodscape. We will explore the day-to-day experience of food, including travel to procure food and the influence of family and community members. We will also investigate the connection people make between food, health and well-being, and the environment.

The focus groups will be held at local venues, such as community church halls or appropriate business outlets; will be conducted by two facilitators; and will last approximately two hours. Focus groups will be held for male and female participants as well as for lower- and higher-SES participants separately. Each focus group will start with a short introduction to the project, described as research on the food local people eat and how they get it. Using a topic guide, the facilitator will help to guide and explain the questions, a second facilitator will take notes, and the discussions of each focus group will be tape-recorded. The audio recordings will be transcribed verbatim and, if applicable, translated into English.

#### Stakeholder Interviews

At baseline, stakeholder interviews in the intervention area will be oriented around determining how decisions to invest in and situate the mall and hypermarket were made as well as projected impacts in relation to food prices and variety, other food outlets in the area, food supply chains, and health among the local people. At follow-up, interviews will focus on the implementation of the intervention and any important short-term outcomes. In the comparison area, stakeholder interviews at both time points will focus more broadly on the impacts of the changing local foodscape.

The interviews will be held at a location convenient to the stakeholder, likely their place of work. Semistructured interviews will be conducted by two facilitators according to a topic guide and will last for approximately one hour. The interviews will be tape-recorded; the audio recordings will then be transcribed verbatim and, if applicable, translated into English.

#### Foodscape Audit

At baseline and follow-up, systematic on-the-ground data collection will be undertaken to geolocate and categorize food outlets in each of the local study areas. Teams of field workers will systematically walk around the study areas, coding the location and types of establishments and taking photos of food outlets. Data collection will be undertaken using electronic tablets. In addition, we will explore the availability and accuracy of existing data, such as county records of licensed food sellers.

#### Shopper Intercept Survey

At follow-up, shoppers in the hypermarket will be intercepted while they shop and asked a set of standard questions covering basic demographics, the items being purchased on the shopping trip, the mode of transport used to get there, and the main reasons for using the hypermarket. A field worker will administer the survey by interview with the aid of an electronic tablet. It is anticipated that each survey will take 5 to 10 minutes.

#### Data Management

The study will be conducted in accordance with relevant current policies, standard operating procedures, and regulatory requirements for data protection, storage and security, and secure data sharing across sites at the Kenya Medical Research Institute and the University of Cambridge. Each participant will be assigned a unique registration number. A master list linking each participant registration number to identifying details will be stored separately from the deidentified data. There will be secure storage of both paper (ie, locked filing cabinet) and electronic (ie, password-protected database) data at the Kenya Medical Research Institute. Electronic data will be stored on a secure server at the Kenya Medical Research Institute.

#### Quantitative Data

For the household survey, foodscape audit, and shopper intercept survey, data will be captured electronically using preprogrammed forms with existing prompts, codes, and validation rules to help limit missing data and ensure data quality using the mobile app CommCare (Dimagi). Additional quality control checks will be undertaken once these quantitative data are collated in the database.

Raw survey data will be collected, stored, and backed up on restricted-access CommCare cloud servers. Raw data sets will be downloaded by a data manager onto local password-protected computers for additional backup and management. Data cleaning will be undertaken using Stata software (StataCorp), in which data will be checked for inconsistencies, variables manipulated, and new variables derived. A cleaned data set will be generated and stored locally alongside cleaning and analysis files. Cleaned, deidentified data sets will be shared between institutions according to local ethical approval and the terms of a formal data sharing agreement.

#### Qualitative Data

For the qualitative focus groups and stakeholder interviews, all transcripts will be checked for accuracy by specially trained qualitative coders prior to analysis. Transcripts will then be imported into NVivo software (QSR International) for coding.

### Analysis Methods

#### Household Survey

For all quantitative analyses, the level of statistical significance will be set as α<.05. All participants who provide data will be included in analyses, and we will not impute missing data. Net changes between baseline and follow-up will be computed, and significance tests will be conducted using a method appropriate to the distribution of the data. Differences in means will be compared using *t* tests or analyses of variance for normally distributed variables, while medians will be compared using the Wilcoxon rank-sum test or the Kruskal-Wallis test for skewed data. We will further undertake multivariable regression analyses adjusted for important covariates, using models appropriate to the distribution of the data and accounting for clustering by household. For binary outcomes, we will explore the use of logistic regression models, and for continuous outcomes we will consider linear regression models and negative binomial or zero-inflated generalized linear models. Regression estimates and 95% confidence intervals will be reported.

